## Eligibility criteria for patients

### Inclusion criteria

Each hospital will provide clinical, demographic and laboratory data for the last 50 deaths that occurred in the institution. Data from the patient who was discharged alive with a date and time closer to the date of death of the case will be used as controls. Fifty controls will be used per hospital, totaling 100 patients per hospital. Consecutive matching with the closest live high will ensure that any temporal impacts are minimized.

In addition to the general criteria mentioned, the specific inclusion criteria are:

- Patients over 18 years of age;
- Hospital stay for more than 24 hours;

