## Data collection

Data collection will be performed by each hospital using an electronic data collection system designed specifically for the study. The filling will be done by each center based on data from medical records, according to local availability, respecting the maximum period of completion of two years. All data collected will be anonymous, in order to preserve the identity of the participants and guarantee confidentiality. The data to be collected are:

1. Charlson Comorbidity Index )
2. Reason for admission: Scheduled versus unscheduled. Presence of infection as the cause of hospital admission (defined as admission with a primary diagnosis of infectious pathology by ICD 10).
3. Physiological variables: Blood pressure, heart rate, respiratory rate, level of consciousness.
4. Laboratory variables: Renal function (serum creatinine), blood count, C-reactive protein (if available), coagulogram , bilirubin, serum lactate .
5. Result of all cultures (blood, tracheal secretion, urine or other sites) collected during hospitalization.
6. Length of stay in hospital
7. Use of intra-hospital resources

- a. Number of imaging tests performed to elucidate an infectious focus
- b. Need for surgical procedures
- c. Intensive care stay
- d. Use of supportive therapy such as mechanical ventilation, renal replacement therapy, use of vasopressors.

Laboratory and physiological variables will be collected from admission and during the first three days of the patient's hospitalization. In the event of addition, initiation or change of antimicrobial regimen and/or collection of some type of microbiological examination (culture), we will perform physiological and laboratory data collection again for an additional period of three days before and after the date of your occurrence. in order to monitor the occurrence of organic dysfunction associated with a suspected infectious condition (sepsis). In these situations, we will also note:

1. The causative focus of sepsis
2. The antibiotic prescribed and its suitability (i.e., whether the antibiotic prescribed at the initial time was effective against the pathogen that eventually proved to be the cause of the event )
3. Whether or not the infection was associated with a surgical procedure or invasive device (prosthesis infection, catheter-related bloodstream infection, etc. ).

We will also note the occurrence of other clinical complications, such as:

1. Pulmonary thromboembolism

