2. Myocardial ischemia/myocardial infarction
3. Stroke (ischemic or hemorrhagic)

For cases (that is, for hospital deaths), we will collect the information contained in the death certificate (immediate cause and its sequence, as well as contributing causes).

*Definition of the exposure factor:* The exposure of interest is nosocomial sepsis, that is, a nosocomial infection that courses with the occurrence of organic dysfunction. As organic dysfunction, we will consider the presence of at least one of the factors below when starting or changing the therapeutic antimicrobial regimen in a hospitalized patient:

1. Systolic pressure < 90 mmHg or mean pressure < 65 mmHg or pressure drop > 40 mmHg
2. PaO2 /FiO2 ratio <300 or O2 requirement to maintain SpO2 > 90
3. Lowering the level of consciousness
4. Creatinine > 2.0 mg /dL or urine output less than 0.5mL/Kg/h in the last 2 hours
5. Bilirubin > 2mg/dL
6. Platelet count < 100,000mm^3

7. Lactate above the reference value
8. Coagulopathy (INR > 1.5 or APTT > 60 sec )

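### The sepsis exposure does not require organ dysfunction to be new or worse than baseline and gives no onset rule for nosocomial, so stable chronic dysfunction can count as nosocomial sepsis

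*Protocol*

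**What the plan says.** The places below are in the second of the two protocol texts in the file, which carries the patient eligibility criteria.

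- **Exposure** (Data collection, definition of the exposure factor): "The exposure of interest is nosocomial sepsis, that is, a nosocomial infection that courses with the occurrence of organic dysfunction". The next sentence defines only the dysfunction part: "we will consider the presence of at least one of the factors below when starting or changing the therapeutic antimicrobial regimen in a hospitalized patient". A closed list of eight factors follows, including "Creatinine > 2.0 mg /dL or urine output less than 0.5mL/Kg/h in the last 2 hours" and "Bilirubin > 2mg/dL".
- **Data available** (Data collection): "Laboratory and physiological variables will be collected from admission and during the first three days of the patient's hospitalization". When antimicrobials are added, started or changed, or a culture is taken, they are collected again "for an additional period of three days before and after the date of your occurrence".
- **Infection at admission** (Data collection): recorded only through an infectious primary ICD-10 diagnosis.
- **Minimum stay** (Inclusion criteria): "Hospital stay for more than 24 hours".
- **Analysis** (Statistical analysis): the attributable fraction comes from the Miettinen formula, using the proportion with sepsis among non-survivors and daily odds ratios from a weighted mixed logistic model. The Charlson index is in both the weight model and the outcome model. Infection at admission is listed only for the outcome model. Two sensitivity analyses use graded certainty of sepsis.
- **Adjudication** (Data management): audit and adjudication of sepsis are planned in all cases, without stated criteria.

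**The concern.** The Introduction describes sepsis as an infection that produces organ dysfunction. The operational rule asks only whether a factor is present when treatment starts or changes. A patient with renal failure, cirrhosis or anticoagulant treatment who already lies beyond a cut-off meets the dysfunction part without the infection having caused anything. If that patient has any treated nosocomial infection, however minor, the exposure is positive.

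There is also a question of timing. Without an onset rule, an antimicrobial start early in a stay that need only exceed 24 hours cannot be assigned reproducibly across 30 hospitals to a hospital-acquired or an admission infection. The ICD-10 flag does not pick up an admission infection coded as a secondary diagnosis.

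The primary objective is mortality attributable to nosocomial sepsis. Everyone labelled septic among the deaths enters the proportion in the Miettinen formula, so false-positive labels go straight into the main result.

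**Working it through.** **1. The eight factors, sorted by whether they need a change.**

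| Factor | Needs a change from an earlier value? |
|---|---|
| Blood pressure | Only in one alternative ("pressure drop > 40 mmHg"); the systolic and mean limits are absolute |
| Consciousness | Worded as a lowering |
| Oxygenation or oxygen need | No |
| Creatinine or urine output | No |
| Bilirubin | No |
| Platelets | No |
| Lactate | No |
| INR or APTT | No |

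Six of eight have no change element. Admission values are collected, but the rule does not use them as a baseline.

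**2. The plan's own figure.** The sample size section assumes 15% nosocomial sepsis in controls and an odds ratio of 1.4, so the prevalence in deaths is 0.15 × 1.4 / (0.85 + 0.15 × 1.4) = 0.21/1.06 = 19.8%. With two-sided alpha 0.05 (assumed, as it is not stated), 90% power and 1:1 allocation, the continuity-corrected total is 2 × 1,345 = 2,690, in line with the stated 2,700. The sample size arithmetic is not in question.

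**3. Formula.** Let Pc and P0 be the exposure prevalence in deaths and controls. The crude Miettinen fraction is

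AF = Pc(OR − 1)/OR = 1 − (1 − Pc)/(1 − P0).

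If the rule wrongly labels a share f_d of truly unexposed deaths and f_c of truly unexposed controls, then

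1 − AF_obs = (1 − AF) × (1 − f_d)/(1 − f_c).

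The direction of the error therefore depends only on whether f_d is above, equal to or below f_c.

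**4. Illustration.** All prevalences and false-positive rates here are assumptions; the protocol gives no false-positive rates. True prevalence is 20% in deaths and 10% in controls.

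| f_d / f_c | Pc observed | P0 observed | OR | AF |
|---|---|---|---|---|
| 0 / 0 | 0.200 | 0.100 | 2.25 | 1 − 0.800/0.900 = 11.1% |
| 5% / 2% | 0.240 | 0.118 | 2.36 | 1 − 0.760/0.882 = 13.8% |
| 10% / 3% | 0.280 | 0.127 | 2.67 | 1 − 0.720/0.873 = 17.5% |
| 5% / 5% | 0.240 | 0.145 | 1.86 | 1 − 0.760/0.855 = 11.1% |
| 2% / 5% | 0.216 | 0.145 | 1.62 | 1 − 0.784/0.855 = 8.3% |

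With true prevalences of 30% and 10%, the fraction of 22.2% becomes 24.6% (5%/2%) or 27.8% (10%/3%).

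**5. Equal rates at the design values (15% and 19.8%).** The crude fraction stays at 0.198 × 0.4/1.4 = 5.7%. With 1,500 per group and no continuity correction, power for the simple comparison of proportions changes as follows.

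| Equal false-positive rate | OR | Power |
|---|---|---|
| 0 | 1.40 | 94% |
| 5% | 1.31 | 86% |
| 10% | 1.26 | 78% |
| 20% | 1.19 | 61% |

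**The case against.** **Admission infections.** A reader might infer that the rule classes community infections treated from day 1 as exposure. The text does not support that. The sentence before the list requires a nosocomial infection, the list defines only the dysfunction part, and the primary objective is limited to nosocomial sepsis. What stands is that nothing says how nosocomial is decided, and the ICD-10 flag is incomplete.

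**Any abnormal value.** It is also tempting to say that any abnormal value at any antimicrobial start counts. That is too broad. The list is closed, the regimen must be therapeutic, a nosocomial infection is needed, the patient must actually cross a cut-off, and two items include wording about change.

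**Safeguards.** Adjudication, Charlson and admission-infection adjustment, calculation by admission type and the graded sensitivity definitions all reduce the problem. None states a baseline or onset criterion for the primary exposure. Adjustment for comorbidity does not relabel a misclassified patient. If adjudication in all cases means deaths only, which is how the protocol uses the word cases elsewhere, it would also treat deaths and controls differently.

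**Direction.** The document does not establish that the fraction is inflated. Chronic organ disease makes more false positives among deaths plausible, but controls treated for infection and discharged alive can be mislabelled too. This objection stands.

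**Level of detail.** An SAP or adjudication manual, not shown here, could hold an onset window. That weakens the onset half. It does not remove the first half, because the protocol does state the dysfunction rule and states it without a newness condition.

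**Conclusion.** The point holds in a limited form. As written, the dysfunction part of the primary exposure is met by stable chronic dysfunction, contrary to the protocol's own concept of sepsis. The missing onset rule for nosocomial is a secondary gap: admission infections are left unseparated in practice, but they are not defined as exposure.

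The size and direction of the error cannot be taken from the document. Under the assumed rates an 11.1% crude fraction could read anywhere from 8.3% to 17.5%. With equal rates the fraction is unchanged, but the odds ratio and power fall. These figures are unadjusted and ignore the weighting, the covariates and the daily odds ratios, so they show the mechanism and do not predict the result. The change is worth making because it is cheap and protects the primary estimate.

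**What to change.** In the definition of the exposure factor, for the primary exposure variable:

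1. Count a factor only if it is new or worse than the patient's admission value or, where that is unsuitable, the earliest value in the three-day window before the event.
2. State a default for events with no earlier value, and report how often it is used in deaths and in controls.
3. State an onset rule for nosocomial that excludes treatment of an infection already present at admission.
4. Apply the same rules, and the same adjudication, to deaths and controls.
5. Keep the current rule as a sensitivity definition.

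**Cost.** This is mainly a change in how the variable is derived. Creatinine, bilirubin, blood count, coagulation tests, lactate, blood pressure and consciousness are already on the collection list. Oxygenation and urine output are not, so those two criteria need either added fields or the default. Records depend on local availability, so some events will lack a baseline, and a baseline taken just before the event may miss sepsis that was already developing. Running the current rule alongside shows how much these choices matter.

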## **Statistical analysis**

Traditional univariate analysis comparing groups (case and control) with respect to the variables described above will be performed using t-test or Mann-Whitney test for continuous variables (as appropriate depending on the occurrence of normality) and Chi-square test for comparison of proportions.

The following approach will be used to calculate attributable fraction calculation for each admission type: The inverted probability weights (IPW) for each patient will be calculated, representing the cumulative risk of the patient acquiring sepsis during hospitalization, under a multivariable logistic regression analysis including baseline age, Charlson Comorbidity Index, and a time-dependent variable for the occurrence of clinically relevant events. We will estimate the association between sepsis occurrence on hospital mortality within 28 days through a mixed logistic regression model weighted by IPW. The model will include the participant center as a random intercept, and age, Charlson Comorbidity Index, infection at admission, IPW, and the accumulated dependent time variables of sepsis occurrence and clinically relevant events with their interaction with time (modeled with a third-degree polynomial). From the daily odds ratios

estimated by the model, the Miettinen formula will be used to calculate the attributable mortality of sepsis:

$$P_{c_i} * \frac{OR_i - 1}{OR_i}$$

*i = day,  $P_c$  = proportion of patients that had sepsis among non – survivors*

We will also present the marginal effect of having one sepsis episode on the whole period, with an estimate of average attributable fraction obtained from the model. All analyses will be performed using the R software

*Sensitivity analysis:* Different definitions of sepsis will be explored; the same analysis method described above will be used for different definitions as sensitivity analyses. An internal consensus was created within the steering committee on probability degrees of sepsis according to combinations of use of antibiotics, organ failure, results of cultures, and occurrence of clinically relevant events. Two sensitivity analyses will be made, one estimating the attributable fraction considering definitive, very probable, and probable sepsis, and a second sensitivity analysis considering only definitive and very probable sepsis.

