| Primary Purpose                   | To measure attributable mortality from nosocomial sepsis in hospitalized patients in Brazil.                                                                                                                                                                                                                                                                                                                           |
| secondary objectives              | 
 
1. Assess length of hospital stay in patients with or without sepsis
 
2. Assess mortality attributable to other hospitalization complications (infarction, stroke, pulmonary thromboembolism )
 
3. Evaluate the quality of completion of medical records
 
4. Assess the quality and consistency of filling in the hospital death certificate
 
 |
| Eligibility of cases and controls | Each hospital will provide clinical, demographic and laboratory data for the last 50 deaths that occurred in the institution. Data from the patient who was discharged alive with a date and time closer to the date of death of the case will be used as controls.                                                                                                                                                    |
| sample size                       | 30 hospitals, 100 patients in each hospital (50 cases and 50 controls), totaling 3,000 patients                                                                                                                                                                                                                                                                                                                        |

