### Sample size

The sample size calculation was performed using the Fleiss , Tytun and Ury method to estimate the power of a two-tailed test for proportion difference using the Hmisc package of the R software (version 3.5.0). The sample size was estimated for a power above 90% to detect an *odds ratio* of at least 1.4 assuming an incidence of nosocomial sepsis in controls of 15%. Two thousand seven hundred patients would be needed. We have chosen to round the number to 3,000 in order to ensure a safety margin.

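### The stated power above 90% belongs to one pooled comparison, but the attributable fraction is calculated for each admission type, and the types cannot both reach 90%

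*Protocol*

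**What the plan says.** The document holds two protocol texts. The point lies within the later one, which adds eligibility criteria for patients.

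- **Sample size.** The calculation concerns "the power of a two-tailed test for proportion difference". It states "The sample size was estimated for a power above 90" per cent, for an odds ratio "of at least 1.4 assuming an incidence of nosocomial sepsis in controls of 15" per cent. The result is "Two thousand seven hundred patients would be needed", rounded up to 3,000. The synopsis table gives the layout: "30 hospitals, 100 patients in each hospital (50 cases and 50 controls), totaling 3,000 patients". No alpha and no split by admission type is given.
- **Statistical analysis.** The description of the main analysis opens with "The following approach will be used to calculate attributable fraction calculation for each admission type". The weighting model uses age, the Charlson index and clinically relevant events. The outcome model uses age, the Charlson index, infection at admission, the weights, sepsis and clinically relevant events over time, and a random intercept for centre. Admission type is in neither list.
- **Data collection.** The only classification of admission is "Reason for admission: Scheduled versus unscheduled", with infection as the cause of admission recorded beside it.
- **Study objectives.** The primary objective is the mortality attributable to nosocomial sepsis in hospitalized patients in Brazil, with no division by admission type.

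**The concern.** The sample size section and the analysis section describe different comparisons. The first has 1,500 deaths against 1,500 discharges. The second has one calculation per admission type, each with fewer patients. The stated power is a property of the first and does not carry over to the second.

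The objective is also left without a named estimate. It asks for one figure for hospitalized patients overall, while the analysis yields one per type and gives no rule for combining them. The average attributable fraction mentioned at the end of the method does not clearly fill the gap: as worded, it summarises the whole period and says nothing about combining types.

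The earlier text in the same document shows how this may have come about. There, type of admission was a predictor in a single logistic regression, which matched a pooled sample size. The later text calculates by type and keeps the sizing inputs and result unchanged. The finding does not rest on that comparison, because the two sections conflict within the later text alone.

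At stake is the accuracy of a stated design property, and clarity about which number answers the primary question.

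**Working it through.** **Inputs**

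- From the Sample size section: two-sided test of two proportions, odds ratio 1.4, control proportion p0 = 0.15.
- From the synopsis: 1,500 cases and 1,500 controls.
- Assumed: alpha 0.05 two-sided (not stated, but it reproduces the protocol's figure); two admission types, scheduled and unscheduled (inferred from Data collection); within each type, equal cases and controls and 15% control sepsis.

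**Case proportion.** The odds are 1.4 × 0.15/0.85 = 0.2471, so p1 = 0.2471/1.2471 = 0.1981. The difference is d = 0.0481 and the mean proportion is p̄ = 0.1741.

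**Formula**, with n per group and no continuity correction:

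Power = Φ{ [d − 1.96·√(2p̄(1−p̄)/n)] / √([p0(1−p0) + p1(1−p1)]/n) }

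**Reproducing the protocol's figure**

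- 90% power needs about 2,606 patients in total (2,690 with continuity correction).
- 2,700 patients (n = 1,350): (0.0481 − 1.96 × 0.01459)/0.01456 = 1.34, power 91.0%.
- 3,000 patients (n = 1,500): (0.0481 − 1.96 × 0.01384)/0.01382 = 1.52, power 93.6%.

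The protocol's 2,700 for power above 90% is therefore right for the pooled comparison.

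**The same method by admission type.** For a type holding half the patients (n = 750): (0.0481 − 1.96 × 0.01958)/0.01954 = 0.50, power 69.1% (about 66.6% with continuity correction). For other shares of the 3,000:

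| Share of smaller type | Power, smaller type | Power, larger type | Odds ratio detectable with 90% power, smaller type |
|---|---|---|---|
| 50% | 69.1% | 69.1% | 1.55 |
| 40% | 59.4% | 76.8% | 1.62 |
| 30% | 47.7% | 82.9% | 1.74 |
| 20% | 34.2% | 87.5% | 1.95 |
| 10% | 19.4% | 91.0% | not computed |

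A type reaches 90% once it holds 2,606/3,000 ≈ 87% of the patients. The other type then has about 13%, and its power is roughly 25% or less. The smaller type can never hold more than half, so about 69% is its ceiling under these inputs.

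**Sensitivity to the two within-type assumptions**, for a type of 1,500 patients (even split):

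- *Control sepsis in the type.* At 5%, 10%, 15%, 20% and 25% the power is 33%, 55%, 69%, 78% and 83%.
- *Balance of cases and controls.* Controls are chosen by closest discharge date and time, so balance within a type is not assured. The two standard errors become √(p̄(1−p̄)(1/n0 + 1/n1)), with p̄ weighted by group size, and √(p0(1−p0)/n0 + p1(1−p1)/n1). With 1,200 cases and 300 controls the power is 48%; with 1,050 and 450, 60%; with 1,000 and 500, 63%; with 500 and 1,000, 65%.

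None of these variants brings a type with half the patients to 90%.

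**The case against.** Several points on the other side stand.

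- **There is no arithmetic error.** The sample size figure reproduces, and that section never says its power applies to each type. This is an inconsistency of scope between two sections.
- **A reader might infer that power above 90% needs all 3,000 patients pooled.** It does not. About 2,606 are enough, and a type with about 87% of the patients would get there. The documents give no split that excludes this. What holds is narrower: the two types cannot both reach 90%.
- **A reader might take 69% as the power of the type-specific analysis.** It is conditional on the split, the control prevalence and the case-to-control balance within a type, and none of these is given.
- **A reader might expect a non-significant result, probably for scheduled admissions, to be misread against the 90% claim.** The documents do not support this. The objective is estimation, no test or threshold is set for a type-specific fraction, and nothing says that scheduled admissions are the smaller group.
- **The check uses the protocol's simple test.** The planned analysis takes daily odds ratios from a weighted mixed model and applies the Miettinen formula. The check does not give the power of that model or the precision of the fraction. A further loss from weighting is plausible but was not calculated.
- **Admission type is not defined in the analysis section.** Scheduled versus unscheduled is an inference. Infection at admission is already a covariate, which makes it a less likely stratum.

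It can also be said that ranking pooled and type-specific estimates belongs in an analysis plan. That is only partly persuasive, because this protocol itself fixes both the sample size and the unit of analysis, and those two disagree.

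**Conclusion.** The point holds as a consistency finding that should be corrected. The stated power belongs to a pooled comparison, the analysis is described by admission type, and no pooled estimate is named for an objective that concerns all hospitalized patients. With two types and the protocol's own method and effect size, the types cannot both have 90% power. The smaller has at most about 69%, and 34% to 59% if it holds 20% to 40% of the patients. At an even split, the figure moves between about 33% and 83% for control sepsis of 5% to 25% in the type, and between about 48% and 65% for the case-to-control imbalances examined. Confidence is high in the mismatch and lower in any single power figure.

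**What to change.** In the Statistical analysis section, name the pooled attributable fraction, adjusted for admission type, as the primary result, and say that the power in the Sample size section refers to it. Define admission type there, and report the type-specific fractions as secondary, with confidence intervals.

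If the type-specific fractions are meant to be primary, restate the power in the Sample size section by type, with the assumed split.

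Either change is protocol wording and needs no extra patients. The cost is a less favourable stated power for the type-specific results.

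### The sepsis weight is described as one whole-stay risk per patient and is also entered as a covariate; as written it does not balance septic and sepsis-free patient-days

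*Protocol*

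**What the plan says.** The protocol file holds two texts. The point concerns the later one, section Statistical analysis.

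- **Weight.** "inverted probability weights (IPW) for each patient will be calculated, representing the cumulative risk of the patient acquiring sepsis during hospitalization".
- **Weight model.** A "multivariable logistic regression analysis including baseline age, Charlson Comorbidity Index, and a time-dependent variable for the occurrence of clinically relevant events".
- **Outcome model.** The target is "hospital mortality within 28 days through a mixed logistic regression model weighted by IPW", with a random intercept for centre.
- **Outcome-model covariates.** "age, Charlson Comorbidity Index, infection at admission, IPW, and the accumulated dependent time variables of sepsis occurrence and clinically relevant events". The weight is therefore used twice, once as a weight and once as a regressor.
- **Time scale.** The model contains "the accumulated dependent time variables of sepsis occurrence and clinically relevant events with their interaction with time". It yields daily odds ratios, and from those "estimated by the model, the Miettinen formula will be used to calculate the attributable mortality of sepsis".

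The section does not mention the probability of remaining sepsis-free, the exposure history actually observed, or accumulation only up to the day being analysed.

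**The concern.** An inverse-probability weight must invert the probability of the exposure history that the patient actually had. The description departs from this in three ways.

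1. **Probability.** It refers to the risk of acquiring sepsis for every patient. A patient who stayed sepsis-free needs the inverse of the probability of staying free.
2. **Time span.** It refers to the whole hospitalization, while the outcome model is daily. A day-2 record would carry a weight that depends on how many days followed. Length of stay may itself be a consequence of sepsis and is tied to the outcome.
3. **Double use.** Entering such a weight as a covariate conditions the daily model on later stay, and a weighted model does not need it.

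At stake is the primary estimate, since the daily odds ratios go directly into the attributable fraction.

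**Working it through.** **Plan's own figures.** The protocol gives no number for the weights. Its one reproducible figure is the sample size, which aims at more than 90% power and states its effect and exposure as "of at least 1.4 assuming an incidence of nosocomial sepsis in controls of 15" percent. With two-sided alpha 0.05 (assumed, as it is not stated) and a continuity correction, this needs 1,345 per group, or 2,690 in total, in line with the stated 2,700. The point does not touch that figure. It does supply an exposure rate for step 5: odds in cases = 1.4 × 0.15/0.85 = 0.247, so 0.247/1.247 = 19.8% of cases exposed.

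**1. Weight for a sepsis-free patient with risk p.** As written 1/p; needed 1/(1−p).

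| p | As written | Needed |
|---|---|---|
| 0.05 | 20 | 1.05 |
| 0.15 | 6.67 | 1.18 |
| 0.40 | 2.5 | 1.67 |

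The ranking is reversed: low-risk patients receive the largest weights.

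**2. Balance and odds ratio, exact example with no sepsis effect.** Assumed: two equal strata, sepsis risk 5% and 30%, death risk 10% and 40% whatever the sepsis status.

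- Crude: septic odds of death (0.005 + 0.12)/(0.045 + 0.18) = 0.556; sepsis-free odds (0.095 + 0.28)/(0.855 + 0.42) = 0.294. Odds ratio 1.89.
- Weight 1/p for everyone (20 and 3.33): septic odds 0.5/1.5 = 0.333; sepsis-free odds (1.9 + 0.933)/(17.1 + 1.4) = 0.153. Odds ratio 2.18.
- Weight 1/p if septic, 1/(1−p) if not: both odds 0.333. Odds ratio 1.00.

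The low-risk share of septic against sepsis-free patients is 0.05/0.35 = 14% against 0.95/1.65 = 58% unweighted. It is 50% against 19/21.33 = 89% with 1/p for everyone, and 50% against 50% with the observed-exposure weight. The weight as written leaves the groups about 39 points apart, against 43 without any weight.

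**3. Time span.** At an assumed daily sepsis risk of 1%, the inverse of the cumulative risk is 1/(1 − 0.99²) = 50 for a 2-day stay and 1/(1 − 0.99²⁸) = 4.1 for a 28-day stay. The same day-2 record changes weight about twelvefold according to later stay.

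**4. Effect after outcome-model adjustment.** This is a 28-day daily simulation with true sepsis odds ratio 1.0, eight data sets per setting, adjusted for age, Charlson index and events. Monte Carlo 95% limits are in brackets. All rates are assumed. Centre intercept, infection at admission and the sepsis-by-time interaction were left out.

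| Setting | Unweighted | 1/whole-stay risk | Same, weight also a covariate |
|---|---|---|---|
| Full cohort, stay unaffected | 0.97 (0.91–1.03) | 1.01 (0.94–1.09) | 0.88 (0.82–0.95) |
| Case-control, stay unaffected | 0.97 (0.93–1.02) | 0.97 (0.89–1.05) | 0.83 (0.76–0.91) |
| Full cohort, sepsis prolongs stay | 1.04 (0.98–1.09) | 1.31 (1.22–1.41) | 1.15 (1.07–1.24) |
| Case-control, sepsis prolongs stay | 0.85 (0.82–0.87) | 0.91 (0.84–1.00) | 0.79 (0.72–0.87) |

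A separate null case-control simulation gave 0.92 to 1.09 for the weight as written, 0.77 to 0.81 with the weight also a covariate, and 0.88 to 0.98 for the standard day-specific weight.

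Correcting only the complement while keeping the whole-stay risk is no remedy. In four runs per setting, that weight gave null odds ratios of 2.3 to 3.1. The protocol does not describe that variant; it only shows that the time span must be corrected too.

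**5. Into the Miettinen formula.** Illustration with one odds ratio and Pc = 0.198. An odds ratio of 1.31 gives 0.198 × 0.31/1.31 = 4.7%. An odds ratio of 0.79 gives 0.198 × (−0.21)/0.79 = −5.3%. The true value is 0. The design odds ratio of 1.4 would give 0.198 × 0.4/1.4 = 5.7%.

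**The case against.** The strongest defence is that the sentence is loose rather than a formula. It names a standard technique, says what the weights represent, and never writes the inverse of whole-stay risk. Beside a time-dependent predictor and daily effects, cumulative can mean accumulated to each day. The superseded text in the same file planned a marginal structural model, which suggests that standard weights may be intended, and an analysis plan not shown may define them. This stands so far as it goes: a standard weight is not excluded. It cannot be assumed either, because the sentence refers to each patient, to acquiring sepsis and to the hospitalization, and the weight reappears as a covariate.

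A reader might go on to infer that confounding is left in place, or that the plan creates a spurious sepsis odds ratio away from the null. The documents do not support either.

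- Age, Charlson index and clinically relevant events, which are all the weight-model variables, are also in the outcome model, with infection at admission and a centre intercept. With that adjustment, stay unaffected and the weight not a covariate, the weighted null odds ratio was 1.01 and 0.97.
- The upward shift to 1.31 arose in a full cohort. The study takes 50 deaths and 50 live discharges per hospital. Under such sampling, with sepsis prolonging stay, the values were below 1, and 0.85 was already present without weights.

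The condition that sepsis prolongs stay is not far-fetched. The Introduction says complications lengthen hospitalization, and length of stay by sepsis status is the first secondary objective.

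**Conclusion.** The description is wrong as written and should be corrected before analysis. The exact example shows without simulation that the inverse of the sepsis risk, given to everyone, does not balance the groups (2.18 against a true 1.00, crude 1.89). The time-span arithmetic shows that early records would depend on later stay.

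How far this reaches the primary result is conditional. With the protocol's covariates in the outcome model, null point estimates for the weight as written ran from about 0.8 to 1.3, with an upper Monte Carlo limit of 1.4. Size and direction depend on whether sepsis prolongs stay, on the case-control sampling and on the weight covariate. In the case-control settings the covariate did more than the weighting: 0.97 became 0.83, and 0.91 became 0.79. These figures are illustrations on assumed rates, not predictions for this study.

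**What to change.** Replace the weight sentence with a definition along these lines: for each patient and day t, the weight is the product over days up to t of the probability of the observed sepsis status given time and no prior sepsis, divided by the same probability given covariate history and no prior sepsis. Sepsis-free days use 1 minus the daily sepsis probability, and the onset day uses the sepsis probability. The factor is 1 after first onset if the exposure is first sepsis; if repeat episodes count, the protocol should say so and extend the product. Nothing observed after day t enters.

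Delete the weight from the outcome-model covariates. Report weighted standardised differences between septic and sepsis-free patient-days.

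The cost is one paragraph, a short change to the weight code and no new data, with some loss of precision compared with no weighting. If standard weights were already intended, the edit only records it.

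The change does not cure distortion from the sampling itself: in the separate case-control simulation the standard weight still gave 0.88 to 0.98 under the null. The daily sepsis probabilities would also have to be estimated from a sample that is half deaths.
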